### Statistics

#### Study hypothesis and sample size

In modern technique of image-guided ISBT for locally advanced uterine cervical cancer, the rate of grade 3 or higher acute non-hematologic adverse effects was reported to be 6.9 % [24]. In the HBT, less applicators are used compared to ISBT and dwell time of each applicator is supposed to be longer in the HBT than in the ISBT and complication is expected to be slightly higher in HBT than in the ISBT according to longer dwell time on each applicator. Therefore, threshold of the rate of grade 3 or higher acute non-hematologic adverse effects which are attributed to the HBT is set to be 10 % in this trial. In phase I part, 20 patients will be enrolled and if the rate of grade 3 or higher acute non-hematologic adverse effects happen in more than 3 patients (>10 %), the trial will be stopped.

In phase II part, it is hypothesized that HBT yields better 2-year pelvic progression-free survival rate than conventional ICBT for tumors which did not show good response to whole pelvic radiation therapy. Historical control data is cited from the publication of Pötter et al. [22] which demonstrated that 2-year pelvic progression-free survival rate of 64 % for patients with uterine cervical cancer whose initial tumor size was larger than 5 cm and were treated with conventional ICBT. If the lower margin of 90 % confidence interval of the 2-year pelvic progression-free survival of the HBT trial is higher than 64 %, the HBT is considered to be more effective than conventional ICBT. In phase II part, the planned sample size is 55 patients including 20 patients enrolled in phase I part, which was calculated based on an expected 2-year pelvic progression-free survival of 80 % and a threshold of 64.8 %, with a one-sided alpha error of 0.05 and a beta error of 0.2.

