**Methods and design:**

Patients with histologically confirmed FIGO stage IB2, IIA2, IIB, and IIIB uterine cervical carcinoma width of which is larger than 5 cm assessed by MRI will be entered to this clinical trial. Protocol therapy is 30-30.6 Gy in 15-17 fractions of whole pelvic radiotherapy concurrent with weekly CDDP (40 mg/m^2^), followed by 24 Gy in 4 fractions of HBT and central shield EBRT up to 50-50.4 Gy in 25-28 fractions. Tumor width is assessed again within one week before the first HBT and if the tumor width is larger than 4 cm, patients proceed to the secondary registration. In phase I section, feasibility of this will be investigated. If less than 10 % out of 20 patients experienced greater than grade 3 acute non-hematologic adverse effects, the study proceeds to phase II part. In phase II part a total of 55 patients will be accrued and the efficacy of the HBT will be investigated comparing with historical control data. If the lower margin of 90 % confidence interval of the 2-year pelvic progression-free survival of the HBT trial is higher than 64 %, the HBT is considered to be more effective than conventional ICBT.

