**Fig. 2 Fig2:**
[figure not shown]
Overview of the protocol study

Figure 3 shows the stages of the HBT study. First 20 patients who proceeded to the secondary registration will be enrolled in phase I part and the safety and tolerability of the HBT will be investigated. If less than 2 out of 20 patients (10 %) develop Grade 3 or higher acute non-hematological adverse effects, the HBT study proceeds to phase II part. In phase II part, 2-year pelvic progression-free survival is compared with historical control. Historical control data is cited from the publication of Pötter et al. [22] which demonstrated that 2-year pelvic progression-free survival rate of 64 % for patients with uterine cervical cancer whose initial tumor size was larger than 5 cm and were treated with conventional ICBT. Therefore, if the lower margin of 90 % confidence interval of the 2-year pelvic progression-free survival of the HBT trial is higher than 64 %, the HBT is considered to be more effective than conventional ICBT.

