### Endpoints

The primary endpoint of this study in phase I part and in phase II part is the rate of acute non-hematologic adverse effects and the 2-year pelvic progression-free survival, respectively.

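### The phase I go/no-go event is not defined consistently: the 10 % limit is set for grade 3+ events attributed to HBT, but the decision rules state no attribution and the abstract's wording excludes grade 3

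*Protocol article*

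**What the plan says.** The article describes the phase I event in five places.

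- **Statistics, threshold sentence:** "grade 3 or higher acute non-hematologic adverse effects which are attributed to the HBT is set to be" 10 %. The grade is 3 or higher and attribution to HBT is required.
- **Statistics, stopping sentence:** the trial stops "if the rate of grade 3 or higher acute non-hematologic adverse effects happen in more than 3 patients (>10" %). The grade is the same, but no attribution is stated.
- **Study design, paragraph on the stages of the study:** "If less than 2 out of 20 patients (10 %) develop Grade 3 or higher acute non-hematological adverse effects", the trial goes on to phase II. The grade is the same, and again no attribution is stated.
- **Abstract, Methods and design:** "If less than 10 % out of 20 patients experienced greater than grade 3 acute non-hematologic adverse effects", the trial goes on. The grade is above 3, and no attribution is stated.
- **Endpoints:** the phase I primary endpoint "is the rate of acute non-hematologic adverse effects and the 2-year pelvic progression-free survival, respectively". Neither grade nor attribution is stated.

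The Therapy protocol section gives weekly cisplatin concurrently with EBRT to all patients. Central-shield EBRT and HBT both start after the first 30-30.6 Gy. The 10 % limit is argued from a 6.9 % rate of grade 3+ acute non-hematologic events reported for image-guided ISBT, raised somewhat because each HBT applicator is expected to dwell longer.

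**The concern.** This count is the phase I primary endpoint and the only gate to phase II that the article describes. The argument for 10 % concerns brachytherapy alone: number of applicators and dwell time. A rule that counts grade 3+ events whatever their cause adds toxicity from pelvic EBRT and cisplatin, and compares the sum with a limit that was not set for it. A rule that counts only events above grade 3 errs the other way and ignores most or many of the events the limit was meant to control, depending on how severe they are.

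If the definition is not settled beforehand, the same 20 patients could lead to proceeding or stopping according to which sentence is followed, and that choice could be made after the events are known.

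**Working it through.** **Inputs from the article.** Phase I size n = 20; reference rate 6.9 %; limit 10 %; proceed if fewer than 2 of 20 have an event (Study design); stop if more than 3 do (Statistics).

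**Inputs assumed, because the article gives none.** b is the rate of grade 3+ events due to EBRT or cisplatin, independent of HBT events, at 5, 10 and 20 %. s is the share of patients with a grade 3+ event whose event exceeds grade 3, at 10, 25 and 50 %.

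**The article's own percentages.** 2/20 = 10 %, so the Study design label fits its count. More than 3 of 20 means at least 4/20 = 20 %, so the label of above 10 % in the stopping sentence does not fit its count; the first count above 10 % is 3/20 = 15 %. The two cut-offs also disagree with each other: with 2 or 3 events, Study design does not proceed and Statistics does not stop. That is a separate matter, but it means both rules have to be carried through the calculation.

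**Formulas.** With X binomial (20, p):

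- fewer than 2: P(X ≤ 1) = (1 − p)^20 + 20·p·(1 − p)^19
- not more than 3: P(X ≤ 3)

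With h the HBT-attributed grade 3+ rate, the counted rate p is:

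- attributed, grade 3+: p = h
- any cause, grade 3+: p = 1 − (1 − h)(1 − b)
- attributed, above grade 3: p = h·s

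**Worked line.** h = 0.069: 0.931^20 + 20 × 0.069 × 0.931^19 = 0.239 + 0.355 = 0.594. With b = 0.05: p = 1 − 0.931 × 0.95 = 0.116.

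**Chance of proceeding at h = 6.9 %:**

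| Event counted | p | Fewer than 2 | Not more than 3 |
|---|---|---|---|
| Attributed, grade 3+ | 6.9 % | 59.4 % | 95.5 % |
| Any cause, b = 5 % | 11.6 % | 31.0 % | 80.6 % |
| Any cause, b = 10 % | 16.2 % | 14.2 % | 58.9 % |
| Any cause, b = 20 % | 25.5 % | 2.2 % | 21.0 % |
| Above grade 3, s = 10 % | 0.7 % | 99.2 % | > 99.9 % |
| Above grade 3, s = 25 % | 1.7 % | 95.4 % | > 99.9 % |
| Above grade 3, s = 50 % | 3.5 % | 85.0 % | 99.6 % |

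**At h = 10 %,** the fewer-than-2 rule gives 39.2 % for attributed events, 19.1, 8.4 and 1.2 % for any cause (b = 5, 10, 20 %), and 98.3, 91.2 and 73.6 % above grade 3 (s = 10, 25, 50 %). The more-than-3 rule gives 86.7 % for attributed events, 67.2, 45.6 and 14.7 % for any cause, and at least 98.4 % above grade 3.

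Two limits apply. If HBT and background events tend to fall in the same patients, the any-cause rate is lower than the formula gives and the gap narrows. The above-grade-3 rows change the grade only; the abstract also states no attribution, so a literal count there would add background events above grade 3 and lower those figures.

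**The case against.** The best defence is that the article never says all-cause. The stopping sentence comes directly after the sentence that requires attribution, and it repeats the 10 % figure, so a reader may carry the qualifier forward. That is a fair reading of the Statistics section. It does not help with Study design, where the go rule stands alone with no attribution nearby. A gate with two defensible readings is itself the defect.

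Other parts of the defence stand:

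- The abstract's wording is probably loose English. The body says grade 3 or higher once under Study design and three times under Statistics. As written it still excludes grade 3, and it needs correcting.
- A reader might take the Endpoints sentence as a further rival rule covering any grade and any cause. It is a short endpoint label with no decision attached, so it is under-specified and not in conflict.
- A reader might infer that chemoradiation toxicity from before the first HBT session is counted. The article does not say so. Phase I takes patients from the secondary registration, which relies on an MRI within one week before the first HBT. The attribution problem rests on the EBRT and cisplatin that run alongside HBT.
- The 6.9 % ISBT benchmark is quoted without saying whether it is attributed or overall. If it is overall, an attributed count would not match the benchmark, although it would match the threshold as worded.

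Causality categories and event windows may well be in the full protocol, and their absence here is no fault. The fault is that the article states the event several times and the statements differ.

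**Conclusion.** The concern holds as an inconsistency in the event behind the phase I decision. The 10 % limit is worded for attributed grade 3+ events, the two decision rules in the body state no attribution, and the abstract's grade differs.

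The consequence is material over the assumed ranges. At an HBT-attributed rate of 6.9 % and the fewer-than-2 rule, dropping attribution takes the chance of proceeding from 59 % to between 31 and 2 %; counting only events above grade 3 takes it to between 85 and 99 %. Under the more-than-3 rule the move is from 95.5 % to between 81 and 21 %, or to at least 99.6 %. At a low background rate under that second rule, the effect is moderate.

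These figures depend on assumed values of b and s and on independence. It would be tempting to combine a high any-cause rate with a very low rate above grade 3 and conclude that wording alone moves the outcome from near-certain stopping to near-certain continuation. The article does not support that, because such rates would not be tied to a common HBT rate and none of them is in the text. Nor does it support saying that the plan has adopted an all-cause count; it has left attribution unstated.

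**What to change.** Before phase I data are assessed, use one event definition, covering grade and attribution, in the abstract, Study design, Endpoints and both sentences of the Statistics section. Make it match the event for which the 10 % limit was set. State whether the 6.9 % benchmark is an attributed or an overall rate, so that the reader can see that limit and benchmark refer to the same thing. Report the other count, attributed or any-cause, descriptively beside the primary one. The relatedness category and the onset window are for the sponsor to define. The differing cut-offs should be reconciled in the same edit; which count is right is not for this review to say.

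The cost is a few lines of wording and, if it is not already collected, an attribution entry for each adverse event. The small downside is that attribution is an investigator's judgement; the descriptive any-cause rate offsets this.

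### The phase I go/no-go boundary is stated inconsistently: 2 events in 20 meet neither the proceed rule nor the stop rule, and at 3 events the stop rule's count and percentage disagree

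*Protocol article*

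**What the plan says.** The protocol article states the phase I decision in three places.

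- **Study design (paragraph on the stages of the study):** "If less than 2 out of 20 patients (10 %) develop Grade 3 or higher acute non-hematological adverse effects, the HBT study proceeds to phase II". This is a rule for proceeding, met by 0 or 1 event.
- **Abstract, Methods and design:** "If less than 10 % out of 20 patients experienced greater than grade 3 acute non-hematologic adverse effects, the study proceeds to phase II part". In counts this is again 0 or 1 of 20, but the event is graded differently: above grade 3, where the other two places count grade 3 or higher.
- **Statistics, Study hypothesis and sample size:** the trial is stopped if "adverse effects happen in more than 3 patients", a count the article labels as above 10 %. This is a rule for stopping, met by 4 or more events. Just before it, the same section sets the threshold for events "which are attributed to the HBT is set to be 10 % in this trial".

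No sentence says what happens at 2 or 3 events, and none ties the stopping rule to the proceeding rule.

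**The concern.** A go/no-go rule on 20 patients should assign every count from 0 to 20 to one decision. Here the proceed rule ends at 1 and the stop rule starts at 4, so the counts between them are unassigned. The percentage attached to the stop rule would start it at 3 instead.

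The Endpoints section makes acute non-hematologic toxicity the primary endpoint of phase I. This decision is also the only gate the article describes before the remaining 55 − 20 = 35 patients are entered. If the unassigned counts were improbable, the wording would matter little, so the question is how likely they are and how far the possible boundaries differ.

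**Working it through.** **Inputs.** n = 20 (Statistics and Study design). Threshold rate 10 % (Statistics). Reference rate 6.9 %, which the Statistics section cites for interstitial brachytherapy. A true rate of 20 % is added as an illustration: it is twice the threshold and is not a figure the plan assumes.

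**Step 1: the plan's own percentages.** 1/20 = 5 %, 2/20 = 10 %, 3/20 = 15 %, 4/20 = 20 %. The Study design pairing of 2 patients with 10 % is correct. The Statistics pairing of more than 3 patients with above 10 % does not reproduce as one boundary: the smallest count above 10 % is 3, whereas more than 3 begins at 4.

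**Step 2: each count under each statement.**

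| Events of 20 | Proceed rule (Abstract count, Study design) | Stop rule, count (Statistics) | Stop rule, percentage (Statistics) |
|---|---|---|---|
| 0–1 | met | not met | not met |
| 2 (10 %) | not met | not met | not met |
| 3 (15 %) | not met | not met | met |
| 4 or more (20 % or more) | not met | met | met |

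Three boundaries can be read from this: stop at 2 or more, 3 or more, or 4 or more.

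**Step 3: chance of continuing.** With X ~ Binomial(20, p), a rule that stops at r or more continues with probability P(X ≤ r − 1) = 1 − P(X ≥ r).

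| Stop at | p = 6.9 % | p = 10 % | p = 20 % |
|---|---|---|---|
| 2 or more | 1 − 0.4059 = 0.594 | 1 − 0.6083 = 0.392 | 1 − 0.9308 = 0.069 |
| 3 or more | 1 − 0.1561 = 0.844 | 1 − 0.3231 = 0.677 | 1 − 0.7939 = 0.206 |
| 4 or more | 1 − 0.0451 = 0.955 | 1 − 0.1330 = 0.867 | 1 − 0.5886 = 0.411 |

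**Step 4: chance of an unsettled count.**

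- 2 or 3 events, P(X ≥ 2) − P(X ≥ 4): 0.4059 − 0.0451 = 0.361 at 6.9 %; 0.6083 − 0.1330 = 0.475 at 10 %; 0.9308 − 0.5886 = 0.342 at 20 %.
- Exactly 2 events, P(X ≥ 2) − P(X ≥ 3): 0.4059 − 0.1561 = 0.250; 0.6083 − 0.3231 = 0.285; 0.9308 − 0.7939 = 0.137. This is the relevant figure if the percentage label governs, because 3 events would then stop the trial.

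The article states no error rates for phase I, so there are none to reproduce.

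**The case against.** **The rules do not strictly give opposite decisions.** A reader might infer that the article proceeds only below 2 events and stops only above 3, so that 2 or 3 events produce contrary instructions. The word only is in neither rule; both are plain if-statements. Read literally, 2 events have no defined outcome. At 3 events the sharper conflict lies inside the Statistics section, between its count and its percentage. This objection stands, and it limits how the point may be put. It does not rescue the rule, because a gate with no outcome at 2 events cannot be applied there.

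**The stopping count may be loose wording for 3 or more.** That would match its percentage, but it is an assumption. It narrows the problem to exactly 2 events without removing it.

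**More than 3 may be the intended boundary.** A reader might infer that this count must be the mistake because the threshold is 10 %. The documents do not support that. A stopping count need not equal the threshold proportion: stopping at 4 or more has a 13.3 % chance of stopping when the true rate is 10 %, which is a usable test. The label is also true of every count above 3; it is just not equivalent to that count. This objection stands, so none of the three boundaries can be ruled out from the text.

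**The article condenses a fuller protocol.** That would excuse an omission. Here the rule is printed three times, and the printed versions do not fit together.

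**Conclusion.** The point holds as an internal inconsistency in the primary phase I decision. Two events in 20 satisfy neither rule. Three events fail the proceed rule and set the stop rule's count against its own percentage. The consequences are material: at a true rate of 10 % the trial continues with probability 39 %, 68 % or 87 % depending on the boundary read, and at 20 % with probability 7 %, 21 % or 41 %. The result falls on 2 or 3 events with probability 36 %, 48 % or 34 % at true rates of 6.9 %, 10 % and 20 %. If the percentage governs, the unsettled probability falls to 25.0 %, 28.5 % or 13.7 %.

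These figures assume 20 evaluable patients with independent outcomes and a common event rate. The 6.9 % belongs to interstitial brachytherapy, and the article expects a slightly higher rate with the hybrid technique, so that column is a reference and not a forecast. Which boundary was intended cannot be determined from the document.

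**What to change.** Reconcile the Abstract, the Study design section and the Statistics section into one complementary integer rule: proceed with k or fewer events in 20, stop with k + 1 or more. Print the percentage that matches that count. Use one event grade throughout, since the Abstract's above grade 3 and the other sections' grade 3 or higher count different events. Beside the rule, state its continuation probabilities at 6.9 %, 10 % and 20 %; the Step 3 table supplies them for k = 1, 2 and 3. The sponsor decides which k was intended.

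The cost is a sentence in each of three places, with no additional patients or data. No further early-stopping provision is needed to correct this point.

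### The phase II success rule tests against 64 %, but the 55-patient sample size was calculated against an unexplained 64.8 %

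*Protocol article*

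**What the plan says.** The Statistics section (Study hypothesis and sample size) gives the historical control as a publication "which demonstrated that 2-year pelvic progression-free survival rate of 64" %. It then sets the success rule for declaring HBT more effective. The rule looks at the lower 90 % confidence limit, and its criterion reads "survival of the HBT trial is higher than 64" %. The Abstract (Methods and design) and the Study design section state the same rule with the same 64 %.

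The last sentence of the Statistics section gives 55 patients, including the 20 from phase I. The alternative there is a rate of 80 %, and the null is introduced by the words "and a threshold of 64.8" %. The type I error is specified as "with a one-sided alpha error of 0.05", and the type II error is 0.2. The value 64.8 % appears nowhere else in the article, and nothing explains how it relates to 64 %.

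**The concern.** One quantity, the null value for the phase II primary endpoint, has two stated values within one section. It cannot be rounding, because 64.8 would round to 65. If 64.8 % was really the design null, then the stated sample size and error rates describe one test and the decision rule applies another.

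What is at stake is the single criterion by which the trial will claim efficacy. A lower confidence limit between 64.0 % and 64.8 % would be a success under the decision rule and a failure under the threshold used for sizing. If that is settled only once the result is known, the conclusion is open to challenge.

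**Working it through.** **Inputs.** All come from the Statistics section: decision threshold and control rate 64 %; sizing threshold 64.8 %; expected rate p1 = 80 %; one-sided alpha 0.05 (z = 1.645), which matches the lower limit of a two-sided 90 % interval; beta 0.2 (z = 0.842); N = 55. I assume that 2-year status is known for every patient unless stated otherwise.

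**Step 1: reproduce 55.** One-sample proportion, normal approximation:

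n = [(1.645·√(p0(1−p0)) + 0.842·√(p1(1−p1))) / (p1−p0)]²

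- p0 = 0.648: √(0.648 × 0.352) = 0.4776, so (0.7856 + 0.3366)/0.152 = 7.383, and n = 54.5, rounded up to **55**.
- p0 = 0.64: √(0.64 × 0.36) = 0.48, so (0.7895 + 0.3366)/0.16 = 7.039, and n = 49.5, rounded up to **50**.

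The exact binomial test gives the same smallest designs.

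| Threshold | Smallest n | Success at | Alpha | Power at 80 % |
|---|---|---|---|---|
| 64.8 % | 55 | ≥ 42 | 0.0459 | 0.803 |
| 64 % | 50 | ≥ 38 | 0.0495 | 0.814 |

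Both standard methods therefore return 55 at 64.8 %, the value the sentence names, and 50 at 64 %. Other approximations at 64.8 % miss 55 (arcsine 52.6; continuity-corrected 60.9). An exponential-survival formula with exactly two years of follow-up gives 54.2 at 64 %, but that does not explain a sentence that itself states 64.8 %. The figure was evidently used in the calculation and is not a slip of the pen for 64 %.

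**Step 2: how the 64 % rule performs with 55 patients.**

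- Normal approximation: power = Φ[(√55 × 0.16 − 0.7895)/0.4] = Φ(0.993) = 0.840. Against 64.8 % it is Φ[(√55 × 0.152 − 0.7856)/0.4] = Φ(0.854) = 0.804.
- Exact: 42/55 is needed; alpha at 64 % is 0.035 and power at 80 % is 0.803.

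**Step 3: error of the 64 % rule if the true control rate is 64.8 %.** The rejection boundary is 0.64 + 1.645 × √(0.64 × 0.36/55) = 0.64 + 1.645 × 0.0647 = 0.7465. The standard error at 64.8 % is √(0.648 × 0.352/55) = 0.0644. The error is 1 − Φ[(0.7465 − 0.648)/0.0644] = 1 − Φ(1.529) = 0.063. In the opposite case, a 64.8 % rule when 64 % is true, it is 0.039.

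**Step 4: does the verdict change?** Lower 90 % limits:

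| Result | Exact | Log-log | Wilson | Linear |
|---|---|---|---|---|
| 41/55 | 0.631 | 0.633 | 0.639 | 0.6488 |
| 42/55 | 0.651 | 0.653 | 0.658 | 0.669 |
| 41/54 | 0.645 | 0.647 | 0.653 | 0.664 |

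With 55 known outcomes, no column separates the two thresholds. Exact, log-log and Wilson limits fail both at 41 and pass both at 42. The linear limit passes both at 41; at 40 it is 0.6285 and fails both. With 54 known outcomes, 41 successes pass at 64 % and fail at 64.8 % by the exact and log-log limits, while the Wilson and linear limits pass both.

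**The case against.** The strongest reply is that the discrepancy does no harm. The decision rule is stated three times at 64 %, which is the control rate the article cites. Sizing against the stricter 64.8 % is conservative for that rule, because 55 exceeds the 50 needed. The 90 % lower limit still corresponds to one-sided 0.05 against 64 %, and with complete follow-up the pass mark does not move. All of this stands. A reader might infer that the trial is underpowered or that its type I error is broken, but the article's own inputs do not support that. The error rises only if 64.8 % is the true control rate, and the article gives 64 %. Even then, the 6 % is the normal-approximation figure; 42/55 judged by an exact limit has error 0.046 at 64.8 %.

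Two further inferences should also be resisted.

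- **That 55 is 50 plus about 10 % for non-evaluable patients.** The article says no such thing, and 55 follows directly from 64.8 %. Nor is 50 a safe target: exact power against 64 % is 0.814 at 50 but 0.793, 0.772 and 0.749 at 51, 52 and 53.
- **That the unnamed interval method or the unstated allowance for losses is a fault.** A condensed article ordinarily leaves both to the full protocol or SAP, which are not shown.

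The reply does not remove the contradiction. The equal pass mark holds at exactly 55 known outcomes, and one fewer is enough to break it under two common intervals. Censoring is realistic for a 2-year survival endpoint.

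**Conclusion.** The inconsistency is real and lies in the current text: success is judged against 64 %, while the 55 patients come from 64.8 %. The article does not show which is the intended control value.

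The practical effect is small. Against 64 %, 55 patients meet the stated alpha and power (0.035 and 0.803 exact; about 84 % power by normal approximation), and with all 55 evaluable the two values lead to the same decision. Two exposures remain. A result such as 41/54, or a Kaplan-Meier lower limit in the 0.8-point gap, would be read differently under the two values. The nominal one-sided error would be about 6 % instead of 5 % if 64.8 % is the true control rate.

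These figures treat 2-year pelvic progression-free survival as a binomial proportion. With censoring, the exact numbers will shift, but the ambiguity remains.

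**What to change.** Before the data are analysed, state one threshold, with its source, in the Abstract, the Study design section and the Statistics section, and make the design figures agree with it.

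- **If 64 % is kept:** correct the sample-size sentence to a 64 % threshold. Say that 50 patients are needed for 80 % power and that the planned 55 give about 84 % by normal approximation (0.80 exact).
- **If 64.8 % is intended:** change the decision rule to 64.8 % in all three places, explain how it derives from the control data, and keep 55 at 80 % power.

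Either route is a change of wording and needs no added patients. The only cost is that the bar is 0.8 percentage points higher if 64.8 % is chosen.
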